### Setting

This study will be conducted in partnership with a high-performing FQHC that serves low-income and uninsured San Diegans and has a long-standing relationship with the lead university. For this study, we will focus on clinics in Central and South San Diego. As shown in Table 1, the 4 target clinics serve primarily Latino and Black patients, and a large proportion report Spanish as their primary language. Preventive healthcare rates for commonly recommended adult preventive screenings and immunizations are low, particularly for blood pressure (*M* = 60.6% across clinics) and flu immunization (*M* = 20.4% across clinics) [18].

**Table 1 Tab1:** FQHC clinic characteristics

	Clinic 1	Clinic 2	Clinic 3	Clinic 4
Total # patients	18,124	20,102	8328	8120
Patient race/ethnicity				
Latino	91.6%	79.0%	61.2%	74.3%
Black	1.3%	3.0%	16.9%	12.1%
Asian	1.5%	4.7%	4.7%	2.2%
White	14.4%	15.0%	29.4%	15.3%
Patient preferred language				
Spanish	70.1%	56.7%	36.0%	48.8%
Adult preventive health services (% of “active” patients who completed a medical visit and had a preventive health service in the past 18 months)				
Blood pressure screening	55.4%	62.3%	58.2%	66.3%
HbA1c screening	78.9%	79.3%	72.8%	81.6%
Flu immunization	25.0%	15.5%	16.2%	24.9%
COVID-19 cases/100,000 (2/20–4/22)	48,219	31,623	34,209	35,716
RATs distributed since 1/22	785 (*M* = 196/month)	499 (*M* = 125/month)	244 (*M* = 61/month)	192 (*M* = 48/month)

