### Power size calculations

The number of participating clusters/clinics and target clinic participant enrollment for the ROIO study design was determined using cluster randomized trial sample size estimation tools. Per the ROIO study design, each clinic cluster will begin in the control group and then cross over into the intervention group at different time points and then continue with the intervention until the end of the study (see Fig. 2). Although it is anticipated that the implementation strategies as outlined by CSAB will undergo some adjustments during the implementation process, the target cluster/clinic sample size estimates are based on a stepped wedge design using serial cross-sectional evaluations of electronic medical records and test kits distributed. It is estimated that the study will have the capacity to distribute 52,000 FDA-authorized rapid antigen tests provided by the San Diego County Health and Human Services and the California Department of Public Health. The primary outcome is the increased distribution of RATs within the communities near each of the 4 clinics. This will be measured using a proxy outcome defined as the proportion of clinic patients visits to the number of RAT kits distributed per month at each participating clinic. Currently, RAT kit distribution among target clinic patients ranges from 7 to 13% (*M* = 9%) with approximately 430 kits being distributed per month between all four clinics. The aim is to increase distribution of test kits to 40% of clinic patient encounters per month, which would result in the distribution of 1822 kits per month during the final treatment sequence. Based on data collected from the phase 1 study, approximately 40% of testing uptake occurred among clinic patients and the remaining 60% from community members even when the intervention was clinic-based. It is anticipated that there will be a similar community uptake during this study. Based on the sequential rollout outlined in the Fig. 2 with rollout for Clinic 1 at month 4, Clinic 2 at month 8, Clinic 3 at month 12, and Clinic 4 at month 16, over the course of the entire study it is anticipated that a total distribution of 20,503 tests, assuming average distribution per clinic. Estimating that this will equal approximately 40% of total increase and the remaining uptake to occur among community members, a total uptake of 58,091 test kits is estimated over the course of the study. Using the Shiny CRT Calculator [24], it was determined that a minimum cluster sample size of 285 across 4 clinics will provide sufficient power (beta > 0.8) to determine an intervention proportion increase of 0.05 to 0.25 assuming the following: stepped-wedge design, cross-sectional sampling structure at each of 4 sequences (approximately every 3 months in the study), 0.5 coefficient of variation in cluster sizes (based on average number of patient encounters per month per clinic), intra-cluster correlation (ICC) of 0.02, for our binary outcome (test or no-test). It was also assumed that there will be an exchangeable cluster correlation structure as SARS-CoV-2 testing demand has been impacted significantly by changes in variant severity and transmissibility.

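### The primary proxy, its 9% baseline, its 40% target and the binary power model do not describe one quantity

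*Protocol article*

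**What the plan says.** The Power size calculations section of the protocol article states the goal first: "The primary outcome is the increased distribution of RATs within the communities near each of the 4 clinics". It measures this by a "proxy outcome defined as the proportion of clinic patients visits to the number of RAT kits distributed per month at each participating clinic".

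The planning figures follow. Baseline: "Currently, RAT kit distribution among target clinic patients ranges from 7 to 13% (*M* = 9%) with approximately 430 kits being distributed per month". Target: "increase distribution of test kits to 40% of clinic patient encounters per month, which would result in the distribution of 1822 kits per month". Patients and community members are then separated, because in phase 1 "approximately 40% of testing uptake occurred among clinic patients and the remaining 60% from community members even when the intervention was clinic-based". The overall kit forecast treats the clinic-based figure as about 40% of the whole and adds community uptake to it. The power calculation in the same paragraph is for a binary tested/not-tested outcome in a stepped-wedge design.

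Three other places bear on this. The vending machine section opens the machines to any member of the public who registers and consents. Table 3 counts the RATs handed out by walk-up testing and vending machines without limiting them to patients. Table 1 gives "Total # patients" and RATs distributed for each clinic. No count of visits or encounters appears anywhere in the article.

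**The concern.** A primary measure should be the same quantity at baseline, at target and in the analysis. Here three features shift.

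- **Direction.** The definition puts visits over kits. Every percentage that follows is kits over encounters.
- **Numerator.** The definition and Table 1 count kits at the clinic, whoever takes them. The 40% target counts kits to patients.
- **Denominator.** The text speaks of patient visits and encounters, but no such count is shown, and the printed figures can be rebuilt without one.

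At stake is whether an observed ratio can be read against the 40% aim at all. An analyst who followed the text with visit counts from the health record would measure something other than what the baseline and target were set on. If kits to non-patients are in the numerator, kits are not a subset of encounters, and a binomial model with one yes/no result per encounter does not describe the data.

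**Working it through.** **Inputs.** From Table 1: patients 18,124; 20,102; 8,328; 8,120 (sum 54,674), and kits per month 196; 125; 61; 48 (sum 430). From Power size calculations: baseline 7 to 13%, mean 9%; target 40%, or 1,822 kits a month; uptake split 40% patients, 60% community.

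**1. Reproduce the plan's figures.** Take encounters per month = patients / 12.

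| Clinic | Patients / 12 | Kits / month | Ratio |
|---|---|---|---|
| 1 | 1,510.3 | 196 | 13.0% |
| 2 | 1,675.2 | 125 | 7.5% |
| 3 | 694.0 | 61 | 8.8% |
| 4 | 676.7 | 48 | 7.1% |
| All | 4,556.2 | 430 | 9.4% pooled; mean of clinics 9.1% |

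Target: 0.40 × 54,674 / 12 = 1,822.5. The range, mean, 430 and 1,822 all match. Other divisors do not fit. Undivided patient totals give a baseline of 0.6 to 1.1% and a target of 21,870. Division by 18 gives 10.6 to 19.5% and 1,215. The later total of 20,503 rests on the same base: 1,822.47 / 4 = 455.6 per clinic-month, and 45 × 455.6 = 20,503.

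**2. Direction.** Read literally, visits over kits is 4,556 / 430 = 10.6 at baseline and 1 / 0.40 = 2.5 at target, so it falls as distribution rises.

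**3. Numerator, on the 40/60 split.**

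- Patients reach 40%: all kits = 1,822.47 / 0.40 = 4,556 a month, and 4,556 / 4,556 = 100%. The result is exact because the target rate and the patient share are both 40%.
- The all-kit ratio reads 40%: patient kits = 0.40 × 0.40 = 16% of encounters.
- Baseline: 9.4% if all 430 kits went to patients. If the split already applied, patient kits = 0.40 × 430 = 172, and 172 / 4,556 = 3.8%.
- Size of the rise: as printed, 1,822 / 430 = 4.2-fold. If the 430 are all kits, the like-for-like rise is 4,556 / 430 (all kits) or 1,822 / 172 (patients), 10.6-fold either way.

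**4. Denominator.** Patients / 12 amounts to one encounter per patient per year. The article gives no visit rate, so the following is an assumption, shown for range only.

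| Visits per patient-year | Encounters / month | 430 kits as a share | 40% in kits |
|---|---|---|---|
| 1 (implied) | 4,556 | 9.4% | 1,822 |
| 2 (assumed) | 9,112 | 4.7% | 3,645 |
| 3 (assumed) | 13,669 | 3.1% | 5,467 |

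Fewer than one visit a year would move the figures the other way.

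**The case against.** The direction is a slip. The next two sentences settle it, since visits over kits cannot give 7 to 13% or 40%. A reader might infer that the trial would register success as a decline, but the article's own figures rule that out. Only the wording needs correcting.

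A patient-only reading is also possible. The baseline sentence refers to clinic patients, the design draws on medical records, the outcome is called binary, and community uptake is added separately. Against this, the Table 1 row behind that baseline has no patient restriction, the definition counts kits at each clinic, and the machines serve the public. The text supports both readings, and that ambiguity is the defect.

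A reader might infer that the measured ratio cannot be compared with the baseline. That is not shown: the baseline appears to use the same unrestricted kit count as the definition. The break lies between baseline and target. A reader might also infer that success could be declared with only 16% uptake among patients. The article has no such rule: 40% is an aim, and effects are to be estimated with multilevel models.

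Two more points stand. The sample size of 285 and the detectable increase of 0.05 to 0.25 do not use the 9%, 40% or 1,822. And because the goal is distribution in the communities, all kits scaled by clinic volume is a defensible rate for a declared proxy. A patient-only primary is not the only sound choice.

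**Conclusion.** The point holds as an inconsistency of definition that should be settled before analysis. The ratio is worded the wrong way round, which is minor. The baseline rests on an unrestricted kit count while the target is patient uptake, and this is the part that matters. On the article's split, the same programme result reads 40% or about 100% depending on whose kits are counted, and the implied rise is 4.2-fold as printed or 10.6-fold like for like. An all-kit ratio is not a bounded tested/not-tested proportion.

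This rests on two assumptions: that the anticipated 40/60 split holds, and that the 430 baseline kits may include non-patients, which the article does not say (hence 3.8% to 9.4% for the patient baseline). That encounters are patient totals / 12 is an inference, but one divisor reproduces every clinic percentage, their mean and 1,822. How far counted encounters would differ cannot be known from the article.

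**What to change.** State the ratio as kits over encounters, and use one numerator and one denominator for baseline, target and analysis, in control and intervention months alike. There are two workable choices.

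1. **All kits.** Count all kits per clinic-month and analyse them as a count or rate with an offset for clinic volume or population. This matches the stated community goal. Restate the target for all kits: about 4,556 a month if 1,822 was meant for patients only, or 1,822 with the community add-on removed if it was meant for everyone.
2. **Patient kits.** Count kits to clinic patients over encounters counted in the health record, as a proportion, and report community kits separately. This needs patient status for both periods.

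Align the power calculation's outcome type with the choice. Recompute the 9%, 40% and 1,822 from actual monthly encounters, or relabel them as shares of total patients / 12.

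The costs are an encounter count from the health record, restated planning figures that may look less favourable, and, for the second choice, a clinic-patient flag that the article does not list among the data collected and that may not exist for kits given out before roll-out.

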#### Data analysis

Quantitative data from study databases will be summarized using simple descriptive statistics including frequencies, measures of central tendency, and variability along with data visualization methods, such as frequency tables, bar charts, line graphs, and scatter plots to understand patterns and characteristics of testing uptake, exposures, and symptoms and to guide adaptive implementation. Missingness in data will be examined via sensitivity analysis and imputation methods will be applied when appropriate. Parametric and non-parametric tests will be employed to compare the survey responses between the clinics while controlling for a variety of demographic and socioeconomic variables, including the FQHC clinic cluster. Data collected at the point of test distribution (collected by study coordinators, promotores, and vending machines) will be used to evaluate implementation strategy effectiveness on testing uptake. Hierarchical multilevel models will be used to ensure the inclusion of random effects, variation between clusters, variation between times within clusters, and the fixed effect of time which will be estimated independently of treatment effect so that systematic change over time will not be mistaken for effect of treatment. This is key, based on significant variations in testing uptake observed during previous COVID-19 variant waves. To account for potential within-clinic correlation, data will be reduced for each cluster to a single observation, and then subject to standard two-sample analyses. Secondary analyses will be conducted to determine the appropriateness of the test type distribution within the context of symptom onset and exposure time frame.

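### The power calculation leaves out the clinic-by-time variation that the uptake model includes, for a reason that does not support doing so; on one reading, power for a 0.05 increase is overstated

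*Protocol article*

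**What the plan says.** Power size calculations (protocol article) treats the trial as a stepped wedge with "cross-sectional sampling structure at each of 4 sequences (approximately every 3 months in the study"), a cluster-size coefficient of variation of 0.5, one ICC of 0.02 and a binary outcome. It states that 285 "will provide sufficient power (beta > 0.8) to determine an intervention proportion increase of 0.05 to 0.25". It then assumes an "exchangeable cluster correlation structure as SARS-CoV-2 testing demand has been impacted significantly by changes in variant severity and transmissibility". The caption of Fig. 2 gives one cluster per treatment sequence.

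Data analysis (under Aim 2 procedures) says the hierarchical models for testing uptake will include "random effects, variation between clusters, variation between times within clusters, and the fixed effect of time". It calls this important because uptake varied during earlier variant waves.

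**The concern.** Under an exchangeable structure, two encounters at one clinic are equally correlated whether they fall in the same period or a year apart. The clinic-by-period variance is then zero, which is the term that Data analysis includes. The two sections therefore assume different variance structures.

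The stated reason does not bridge the gap. A wave that moves all clinics together is absorbed by the fixed time effect and says nothing about exchangeability. A wave that moves clinics differently makes correlation weaker between periods than within them, so the CAC falls below 1. Either way, changing demand is no argument for a constant correlation.

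With one clinic per sequence, clinic-by-period variance does not shrink as more encounters are counted. If power for small increases is overstated, a null or imprecise result after a modest true gain would look more informative than it is.

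**Working it through.** **Inputs from the article.** Four clinics, one per sequence; ICC 0.02; size CV 0.5; baseline 7% to 13%, mean 9%; target 40% of encounters; figure of 285; power above 0.8 (printed as beta).

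**Assumptions not in the article.** Two-sided 5% normal test; five periods (one all-control, then one per roll-out); 285 per clinic-period; +0.05 taken from the 9% mean; CAC from 0.5 to 1.

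**Formula, equal sizes.** Total variance s² = (0.09×0.91 + 0.14×0.86)/2 = 0.10115. Let σ² = s²(1−0.02)/m + 0.02·s²·(1−CAC) and τ² = 0.02·s²·CAC. For this layout the generalised least squares (Hussey-Hughes type) variance of the treatment effect is

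Var = 4σ²(σ² + 5τ²) / (10σ² + 30τ²), and power = Φ(0.05/SE − 1.96).

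- CAC 1, m = 285: σ² = 0.000348, τ² = 0.002023, SE = 0.0151, power 0.91.
- CAC 0.8, m = 285: σ² = 0.000348 + 0.000405 = 0.000752, τ² = 0.001618, SE = 0.0218, power 0.63.

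At CAC 0.8 the clinic-by-period part (0.000405) already exceeds the sampling part (0.000348).

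**With size CV 0.5** (variance averaged over all orderings of relative sizes 1.5, 1.5, 0.5, 0.5):

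| CAC | SE, equal | Power, equal | SE, CV 0.5 | Power, CV 0.5 |
|---|---|---|---|---|
| 1 | 0.0151 | 0.91 | 0.0157 | 0.89 |
| 0.95 | 0.0170 | 0.84 | 0.0179 | 0.80 |
| 0.9 | 0.0188 | 0.76 | 0.0198 | 0.71 |
| 0.8 | 0.0218 | 0.63 | 0.0228 | 0.59 |
| 0.5 | 0.0282 | 0.43 | 0.0290 | 0.41 |

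The CAC 1 row reproduces the stated power above 0.8. The 80%-power detectable increase, 2.80×SE with CV 0.5, is 0.044 at CAC 1, about 0.055 at 0.9 and 0.064 at 0.8. A four-period layout gives 0.83, 0.65 and 0.54 at CAC 1, 0.9 and 0.8.

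**Other readings and sizes (CV 0.5).**

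- 5% rising to 25%, with 285 in total (285/20 = 14.25 per clinic-period): 0.835 at CAC 1, 0.826 at 0.8, 0.818 at 0.5. With 285 per clinic-period: about 1.00 throughout.
- +0.05 from 9%, with 285 per clinic over the whole trial (57 per clinic-period): 0.31 at CAC 1. The stated power is not met even under exchangeability.
- +0.10 from 9%, 285 per clinic-period: 1.00 at CAC 1, 0.98 at 0.8, 0.89 at 0.5.
- 9% to 40%: about 1.00 with 285 per clinic-period, and about 0.97 with 285 in total, at every CAC.
- All visits: 1,822 kits at 40% implies 1,822/0.4 = 4,555 encounters a month, or about 1,139 per clinic, and about 4,556 per four-month clinic-period. For +0.05 from 9%, power is 0.98 at CAC 0.9, 0.85 at 0.8 and 0.52 at 0.5. The SE at CAC 0.8 is about four times the exchangeable value (0.0167 against 0.0040).

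**The case against.** The strongest objection is that the loss rests on one reading. The sentence can equally mean 285 in total and a proportion going from 5% to 25%. That reading also reproduces power above 0.8, suits the words about four clinics, and makes the correlation structure almost irrelevant. This stands: the article does not settle which reading was used, since it names neither the control proportion nor the sampling unit.

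A reader might go further than the document allows in four ways.

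- **That the power claim is simply false, or holds only because the term is zero.** The figure of 285 is a stated minimum. If all visits are analysed, +0.05 from 9% keeps about 0.85 at CAC 0.8.
- **That the trial is underpowered for its aim.** It is not: "The aim is to increase distribution of test kits to 40% of clinic patient encounters per month" is far from the affected range.
- **That the primary model contradicts the power calculation.** No model is labelled primary. The same section also describes reducing each clinic to one observation for two-sample comparison, which does not match the power calculation either. The hierarchical model is, however, the one given for testing uptake, the outcome that was powered.
- **That a particular CAC applies.** None is documented, so no single power figure can replace the printed one.

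None of this repairs the mismatch or the reason given for it. Both are in the text under every reading.

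**Conclusion.** The point holds in a limited form. The power calculation sets to zero a variance that the uptake model includes, and the justification does not support that choice. The numerical consequence is conditional. It is material only if 285 is per clinic-period and 0.05 to 0.25 is a range of absolute increases, and then only near the lower end. There, power for +0.05 from 9% falls below the claimed 80% once the CAC drops to about 0.95, and reaches about 0.59 at 0.8. At that sample size, increases of 0.10 or more are essentially unaffected over CAC 0.8 to 1. If the phrase means 5% to 25%, the change is about 0.01. The results use a normal approximation.

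**What to change.** In Power size calculations:

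1. State whether 285 is per clinic-period, per clinic or in total, and whether 0.05 to 0.25 is a range of increases or a change in proportion. Give the control proportion used.
2. Remove the variant-based justification for exchangeability.
3. Rerun the same calculation with a nested-exchangeable (or decaying) correlation that matches the Data analysis model. Use a stated CAC range, ideally informed by the clinics' monthly RAT counts.
4. Restate the power and the minimum detectable increase across that range.

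The cost is one rerun with one more input and a few reworded sentences. The stated power for small increases may become less favourable. Enrolment and the number of clinics do not change.

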
**Fig. 2 Fig2:**
[figure not shown]
Design matrix structure: one cluster per treatment sequence

## Discussion

This study capitalizes on the unique and complementary methods from community engagement, implementation science, epidemiology, clinical research, and data science to refine, implement, and sustain a multilevel, multicomponent implementation strategy bundle to optimize COVID-19 rapid testing among underserved communities. This study will use a ROIO design to iteratively refine implementation in response to dynamic public health policy and healthcare delivery contexts. This is one of the first pragmatic implementation trials to use an ROIO design, affording opportunities to further develop best practices for adaptive implementation science study designs. Further, although this study prioritizes focus on COVID-19 testing as the evidence-based practice vehicle, the design and methods used can easily be transferred to other public health prevention programs such as sexually transmitted infection testing, flu testing, and viral panels.

Balanced with these strengths are potential challenges and limitations. One challenge will be balancing reach with contextual considerations and competing priorities. Meaningful community engagement to sustainably reduce health disparities requires expertise from community, clinical, and research partners as well as sufficient material resources. The research team has collaborated with the study’s community and clinical partners throughout each step in the phase 1 study and the current study to ensure adherence to rigorous, acceptable, and capacity-building approaches. However, competing organizational and policy priorities may impact study activities. These will be documented in the adaptations tracking form and included in all relevant study analyses. In addition, the research team will rely on the decades of community-engaged participatory action research led by the Global ARC and the quality care and clinical research supported by the partnering FQHC to reduce health disparities in their patient population. The study team will leverage ongoing, weekly meetings to assess any study challenges that arise and jointly make decisions to resolve them. Another limitation is that randomization of clinics or community members will not be possible. Given the duration of the study (2 years), it was only feasible to include 4 clinics with one clinic being the original clinic that was the host of the phase 1 study. Due to the pragmatic and organizational requirements of the FQHC, the clinic roll-out order will be sequenced in a non-randomized fashion, but potential confounding clinic-level and participant-level variables will be collected and included in multilevel models to contextualize findings.

This study has the potential to make a substantial contribution to the field of implementation science through the application of the newly described ROIO design, which will rigorously allow for a flexible and sustainable approach that promotes responsiveness to both the needs of the community and the changing pandemic context while reducing COVID-19 testing disparities. In addition, this study will advance the call for action [25] to explicitly examine the role of implementation vis-à-vis implementation strategies and other health outcomes. It is expected that the study will exert a significant public health impact by increasing optimal COVID-19 testing for unserved or underserved communities near the US/Mexico border.

